#### Control group (Barkley program)

The Barkley program is specifically conceived for parents of children with ADHD, either individually or in groups of 6 to 8 families, with twelve 90-min sessions, occurring twice a month. The objective of this program is to train parents to cope with the difficult situations they encounter, to learn effective control strategies that are coherent and adapted to the “deviant” behavior of their children in order to reduce the intensity of events and their consequences on family life. All this inevitably involves the improvement of family relationships through an essential improvement of the image that parents have of themselves, the image the child has of him/herself, and overall family functioning.

Each session focuses on a “theme” or a particular situation: practical exercises are offered to families to improve communication, adjust the educational responses, analyze the behavior of the child, and anticipate crises in order to avoid them. These practical exercises are practiced at home. A typical session has the following structure: a 30-min review of exercises practiced at home, 60 min: theme of the day’s and new exercises.

The control group facilitator cannot participate in mCBT therapy to avoid bias. The Barkley program is already in use by all participating centers and training per se is not required. Nevertheless, a standardized consensus has been established between the centers to reduce variability before beginning the study and regular meetings are made annually to ensure that the program is followed faithfully.

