## Statistical methods

### Statistical methods for primary and secondary outcomes {20a}

The primary outcome is the change from baseline in the ADHDRS-PI at 5 months. If required for meeting normality, the ADHDRS-PI scores will be appropriately transformed (e.g., Box-Cox transformation). A Student’s test will be used to compare the two groups. If the conditions for use of a Student’s test are not met, a non-parametric Mann-Whitney test will be used. This analysis will be completed by a modeling analysis to take into account clustering effects. Indeed, in our study, randomization to treatment is done on an individual basis; however, the experimental and control treatments are administered to a group so that several individuals receive the intervention together by the same therapists; the observations within the group therapy will likely be correlated within groups (clustering effect). We will use multilevel mixed-effects models to assess the treatment effect on the primary outcome: the ADHDRS-PI score at 5 months by adjusting for cluster effects and ADHDRS-PI score at baseline.

There is no a priori reason for carrying out per-protocol analyses in the present study. All analyses will therefore be performed on the intention-to-treat population. The level of significance is set at *p* < 0.05 (bilateral). The statistical analysis will be performed by the BESPIM using SAS software (SAS Institute, Cary, NC, USA) version 9.4 (or higher) or the R statistics environment (R Development Core Team 2008) version 3.3.1 (or higher).

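### The lead test of the primary outcome assumes independent families, although the plan expects correlation within therapy groups; the multilevel model it already describes should decide the trial

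*Protocol article*

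**What the plan says.** Section {20a} of the Protocol article defines the endpoint: "The primary outcome is the change from baseline in the ADHDRS-PI at 5 months". It then names the comparison: "A Student’s test will be used to compare the two groups". The fallback is also a two-sample test of independent observations: "If the conditions for use of a Student’s test are not met, a non-parametric Mann-Whitney test will be used".

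The clustered analysis comes after these: "This analysis will be completed by a modeling analysis to take into account clustering effects". The section gives the reason itself. Families are randomized individually, but both treatments are delivered to groups by shared therapists, so that "the observations within the group therapy will likely be correlated within groups (clustering effect". The model is specified in outline: "We will use multilevel mixed-effects models to assess the treatment effect on the primary outcome", using the 5-month score adjusted for cluster and for baseline score. The section sets one two-sided 0.05 level and does not attach it to either analysis.

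Three other places bear on the point:

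- The control group section describes the Barkley program as given "either individually or in groups of 6 to 8 families". No group size is stated for the experimental program.
- The sample size section {14} plans 111 children per group, and 124 after a 10% loss.
- Section {20b} treats the ICC as something the trial will estimate. No value is assumed in advance.

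**The concern.** The plan leads with a test whose independence assumption it expects to fail, and gives the analysis that meets the difficulty a complementary role. The Mann-Whitney fallback is no protection, because it needs independence too.

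The two analyses can also disagree. One uses change from baseline and the other uses the 5-month score adjusted for baseline; one ignores therapy groups and the other models them. With a single significance level attached to neither, the order and wording of the section point to the t-test as the one that decides.

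At stake is the false-positive rate of a superiority claim. If therapy groups induce correlation, the t-test's standard error is too small, so a difference is declared more often than the stated 5%. A t-based confidence interval would be too narrow to the same degree. Section {20a} names no interval; this follows because such an interval uses the same standard error.

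**Working it through.** **Inputs from the documents.** Difference 9 points, SD 20.6, two-sided alpha 5%, power 90%, 111 per group, 10% loss (section {14}); 1:1 allocation ({16a}); 6 to 8 families per group (control program section).

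**Assumptions.** The same group size *m* in the experimental arm; ICC from 0.01 to 0.10, all of it induced by the therapy group after randomization.

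**1. The plan's own figure.** n per group = 2 × [20.6 × (1.960 + 1.282) / 9]² = 110.1, rounded up to 111. Dividing by 0.90 gives 123.3, rounded up to 124. Both stated figures reproduce from a formula for independent observations with no design effect. The sample size therefore matches the t-test, not the multilevel model.

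**2. Actual type I error of the t-test.** Design effect DE = 1 + (m − 1) × ICC. Actual error = 2 × [1 − Φ(1.96 / √DE)]. Example with m = 7 and ICC 0.05: DE = 1 + 6 × 0.05 = 1.30; 1.96 / √1.30 = 1.72; error = 8.6%.

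| Assumed ICC | DE, m = 6 to 8 | Actual error | Coverage of a nominal 95% t-interval | SE understated by |
|---|---|---|---|---|
| 0.01 | 1.05-1.07 | 5.6-5.8% | 94.2-94.4% | 2-3% |
| 0.02 | 1.10-1.14 | 6.2-6.6% | 93.4-93.8% | 5-6% |
| 0.05 | 1.25-1.35 | 8.0-9.2% | 90.8-92.0% | 11-14% |
| 0.10 | 1.50-1.70 | 11.0-13.3% | 86.7-89.1% | 18-23% |

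Simulating the t-test on clustered data (20,000 trials per setting, 14 to 18 groups per arm) gives 5.0-5.2% at ICC 0, 6.3-6.7% at 0.02, 8.1-9.5% at 0.05 and 11.2-13.2% at 0.10.

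**3. Which correlation matters.** Because families are randomized individually, the source of the correlation decides whether the error inflates. A second simulation used 8,000 trials per case, 112 families per arm in groups of 7, and four equal centers for convenience (the article lists three).

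| Source of correlation | Actual error of the t-test |
|---|---|
| Sorting into groups on a covariate explaining 10% of variance, no therapy-group effect | about 5% |
| Center ICC 0.10 only | about 4% |
| Therapy ICC 0.02 plus center ICC 0.05 | about 6% |
| Therapy ICC 0.05 plus center ICC 0.05 | about 8% |

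Sorting alone leaves the level intact. Center alone makes the t-test slightly conservative, because allocation is balanced within center and the test ignores that. Inflation remains once the therapy-induced part is appreciable.

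**4. Power of a valid clustered analysis.** Power = Φ(9 / [20.6 × √DE × √(2/111)] − 1.96). With 111 per arm and m = 6 to 8, this gives about 88-89%, 86-87%, 80-83% and 70-76% at ICC 0.01, 0.02, 0.05 and 0.10, against 90% as designed.

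**The case against.** The strongest reply is that clustering is not overlooked. A multilevel model for the primary outcome is prespecified, {20b} extends similar methods to the secondary outcomes, and {20a} never literally calls the t-test the deciding analysis. The article also condenses a fuller protocol, and a statistical analysis plan could rank the two. This stands against any claim that the trial ignores clustering. It does not remove the point, because the article does set an order: the t-test makes the comparison and the model completes it.

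Three stronger readings are tempting, and the documents do not support them.

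- *That the p-value is too optimistic as a matter of fact.* No ICC is given, and at 0.01 the excess is small. The result is conditional.
- *That any correlation within groups inflates the error.* Children's groups are formed by age and school level, and center is a stratification factor. Step 3 shows that correlation from these sources alone does not raise the error.
- *That the control arm may be treated individually, so that clustering differs between arms.* The mention of individual delivery describes the Barkley program in general. Sections {20a} and {22} describe both arms of this trial as group therapy.

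Arm-specific random-effect variances and the exact degrees-of-freedom method are details that an analysis plan may settle. Their absence here is no fault.

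**Conclusion.** The point holds in conditional form. The plan leads the primary comparison with a test that assumes independence, expects that assumption to fail, and ties its significance level to neither of its two analyses. If shared therapy or therapists induce correlation, the lead test does not hold 5%. The excess is minor at an ICC of 0.01 and material from about 0.05. These sizes rest on an assumed ICC and on 6 to 8 families per group in both arms, and they are upper-side figures in so far as ignoring center and methylphenidate strata makes the t-test conservative. The defect lies in which prespecified analysis leads; the valid one is already in the plan.

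**What to change.** Before database lock, reword {20a} so that the multilevel model already described there is the single analysis that decides the primary outcome, and attach the two-sided 0.05 level to it. The model is the 5-month ADHDRS-PI score on arm and baseline score, with a random effect for therapy group, center and methylphenidate treatment as covariates, and a small-sample degrees-of-freedom correction, since there would be only about 14 to 18 groups per arm. Keep the Student's or Mann-Whitney test as a supportive description that cannot overturn the model.

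No new data are needed, because the planned model already requires therapy-group membership. The cost is a somewhat wider interval and, if the ICC is positive, lower power than the 90% in section {14}: about 80-83% at an assumed ICC of 0.05.

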### Eligibility criteria {10}

Participants are children between 7 and 15 years of age presenting an attention deficit and hyperactivity disorder (ADHD Rating Scale Parent Version: Investigator Administered and Scored ADHDRS-PI > 27). The patient and the parents (or legal guardians) give their informed consent and are insured or beneficiaries of a health insurance plan. Regarding treatment, the patient may either be treated with a stable dosage of methylphenidate (not expected to vary in the near future) and remain symptomatic or not be on treatment.

Participation in another trial or study that may interfere with the results or conclusions of this study is a criterion for exclusion, as well as being in a period of exclusion determined by a previous study. Participants whose parent (s) is (are) under judicial protection or is an adult under guardianship are also excluded from the study. In addition, the family cannot be included if it is impossible to properly inform the patient, his/her parents, or legal guardian, and if the patient or parents refuse participation, signature of signed consent, or follow-up procedures. If the investigator suspects the presence of or if there is documented information about an intellectual disability (*IQ* < 70), the patient is excluded. The same applies to patients diagnosed with autism spectrum disorder, psychotic disorder, or bipolar disorder. Finally, the patient should not be involved in cognitive behavioral therapy (individual or group) during the 6 months prior to inclusion and/or have previously participated in this study. Written informed consent is obtained from all participants by the investigators (senior psychiatrists or psychologists) after explaining the purpose and methodology of the study (please see “Declarations”/“Ethics” for more details).

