##### Children group

The first therapist or “leader” runs the session and is considered as the teacher or “facilitator”; the second therapist, the “regulator,” manages the behavior of the children and the group and the organizational aspects. When many children are present, it may be appropriate for three adults to be present, with a second adult regulating “disruptive” behavior and accompanying some children back to calmness while the first regulator concentrates on reinforcement activities.

Children’s groups are formed according to age and school level in order to encourage a sentiment of “belonging.” The vocabulary and techniques used are adapted to each group’s age level and cognitive abilities. The place where children’s sessions take place is important. The room must be simple with few distractors. Seating should be arranged in a U shape to facilitate interaction. Seating should also be quiet in nature (e.g., put tennis balls on chair legs to avoid scraping noises). The session leader is positioned in front of the children next to a paperboard or a slideshow. The regulator freely moves around the room as required or preferentially stays near the back. Seating arrangements for children should be discussed before sessions in order to avoid unwanted interactions. During such sessions with ADHD children, the participating therapists must allow for a certain amount of acceptable agitation and define strategies that help children self-regulate their behavior.

The therapists are encouraged to use a timer. The first 60 min is dedicated to the session, and the last 15 to a summary and review of material covered during the session in order to help emphasize the overall take-home message, to the children’s mission to be performed at home or school, and to self-evaluation and finally an end-of-session game. A bell can be used to signal the beginning and end of each activity, mediation time, etc.

All sessions present the same structure: the group starts with a reminder about the rules, after the mediation “today’s weather and stress thermometer,” then a review of the previous session’s missions. Then comes the sequence of the day which must have a visual support (slides or posters) describing the content of the session. The session ends with a session summary, the new missions, and the child makes a self-evaluation of his behavior. To conclude, there is an end-of-session game.

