##### Parent session

This program is largely inspired by the Russel Barkley program into which have been integrated other tools like mindfulness, acceptance and commitment therapies (ACT), and nonviolent resistance. We adapted these therapeutic techniques in our clinical practice and recommend that they be coupled with a support group for children with ADHD.

The aim of the integrative therapeutic parent group is to offer 16 sessions of integrative therapy on the various spheres of life of the child affected by ADD/ADHD to promote a better quality of life and well-being for the child and family. The parent is placed in a co-therapist position, pledging to initiate change in his/her relationship with his/her child. He/she should not expect an immediate positive reaction from the child. The parent has the responsibility of avoiding any manifestation of verbal or physical violence. Sessions with parents are led by a single therapist trained in cognitive behavioral therapy. Therapists are encouraged to use a visual time cue, such as a timer. The timer can give an indication of the time remaining in the session. For a 75-min session, the first 30 min is devoted to a review of the tasks performed and the last 45 min is devoted to the meeting and presentation of new missions. The place where parental sessions take place is important. The layout of the environment is essential to ensure optimal attentional mobilization, to promote exchanges not only between therapist and parents but also among parents. The room is uncluttered with few distractors, the seats are installed in a U to promote interaction. The therapist is positioned in front of the parents before the paperboard or Powerpoint. The structure of a typical session is described in Table 1.

**Table 1 Tab1:** Structure of a typical session of the Hyper-mCBT program for parents

Structure of the session	
1	Welcome
2	Meditation: today’s interior weather
3	Review of last session’s missions
4	Relaxation
5	Session: the day’s theme
6	Session summary
7	New missions
8	Summary and missions presented in children’s group

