### Methods for additional analyses (e.g., subgroup analyses) {20b}

The models will also provide valuable estimates of intra-cluster correlation coefficients for the different outcomes of our study in the context of behavioral group therapy; these data are necessary to optimize the sample size of further studies in the area of psychological research. Similar methods will be used for secondary outcomes. The temporal evolution of repeated quantitative measures (baseline, 5 months, 8 months) will be compared between groups by a mixed model for repeated longitudinal data.

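### Experimental groups are formed by age and school level, but the multilevel model omits age; if age predicts the 5-month score beyond baseline, this model loses some precision and its ICC mixes age composition with therapy-group effects

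*Protocol article*

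**What the plan says.** - **Group formation, experimental arm.** Under Children group, the article says that children's "groups are formed according to age and school level". Eligibility {10} gives the range: "Participants are children between 7 and 15 years of age". The parents' session is tied to the children's session: the last row of Table 1 reads "Summary and missions presented in" the children's group.
- **Group formation, control arm.** The Barkley program is for parents, "either individually or in groups of 6 to 8 families, with twelve 90-min sessions, occurring twice a month". No age rule is stated, and none is excluded.
- **Analysis of the primary outcome.** Section {20a} first says "A Student’s test will be used to compare the two groups", with Mann-Whitney as the fallback. A multilevel mixed-effects model completes this and assesses "the ADHDRS-PI score at 5 months by adjusting for cluster effects and ADHDRS-PI score at baseline". Age, school level, center and methylphenidate are not named as terms.
- **Use of the ICC.** Section {20b} says "The models will also provide valuable estimates of intra-cluster correlation coefficients for the different outcomes of our study", presents them as needed for sizing later studies, and extends similar methods to the secondary outcomes.

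**The concern.** Randomization is by family and stratified by center and methylphenidate, not age. Children in the experimental arm are placed in groups by age only afterwards. Placing them does not change who is in the arm, so it cannot make the arm mean more variable. It does make group means differ if older and younger children have different 5-month scores at the same baseline score. A random-intercept model without age has only one place for that difference, the therapy-group variance.

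Two things follow. The standard error of the treatment effect from this model becomes larger than the sampling variation warrants. And the ICC, a declared product of the trial, no longer describes therapy-group effects alone. The sample size in {14} carries no allowance for clustering, so the one stated analysis that handles clustering has little precision to give away.

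**Working it through.** **1. The plan's own figure.** Section {14}: difference 9, SD 20.6, two-sided alpha 5%, power 90%. n = 2 × ((1.960 + 1.282) × 20.6 / 9)² = 110.1, so 111 per arm; 111 / 0.90 = 123.3, so 124 per arm and 248 in all. The figures reproduce, and the present point does not change them.

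**2. Assumptions, none of them given in the article.** 16 groups of 7 per arm (112 children, close to 111; 7 is the middle of the 6 to 8 families stated for Barkley groups, and no size is stated for the children's groups). True ICC r = 0.05. Outcome variance after baseline set to 1. R² is the share of it explained by age, taken from 0 to 10%. Control groups are not sorted.

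**3. Closed form under full sorting.** Nearly all the age variance lies between experimental groups, so the ICC without age is about 0.05 + R² in that arm and 0.05 in control. A model with one common variance sees about p = 0.05 + R²/2.

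- SE reported without age: √[2(p/16 + (1 − p)/112)]
- True sampling SD without age: √[2(0.05/16 + 0.95/112)] = 0.1524, whatever R² is
- SE with age: √[2(0.05/16 + (0.95 − R²)/112)]

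| R² | SE without age | True SD | SE with age | Excess from false clustering | Ordinary covariate gain | Total ratio |
|---|---|---|---|---|---|---|
| 0 | 0.1524 | 0.1524 | 0.1524 | 1.000 | 1.000 | 1.000 |
| 1% | 0.1541 | 0.1524 | 0.1518 | 1.011 | 1.004 | 1.015 |
| 2% | 0.1558 | 0.1524 | 0.1512 | 1.023 | 1.008 | 1.031 |
| 5% | 0.1609 | 0.1524 | 0.1494 | 1.056 | 1.020 | 1.077 |
| 10% | 0.1690 | 0.1524 | 0.1464 | 1.109 | 1.041 | 1.155 |

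**4. Simulation (REML random intercept, 600 trials per setting).** Ratio of mean model SE without age to that with age:

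| R² | Full age sorting | Cohorts of 14 split by age into two groups | One group per cohort, no sorting |
|---|---|---|---|
| 0 | 1.00 | 1.00 | 1.00 |
| 1% | 1.01 | 1.01 | 1.00 |
| 2% | 1.03 | 1.02 | 1.01 |
| 5% | 1.07 | 1.06 | 1.02 |
| 10% | 1.15 | 1.12 | 1.04 |

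The first column agrees with the closed form. The last column, where nothing is sorted, matches the ordinary covariate gain. Under full sorting, model SE over empirical SD without age was 1.02, 1.04 and 1.11 at R² of 2%, 5% and 10%. The Monte Carlo error of an empirical SD from 600 runs is about 1/√1200 = 3%, so only the last of these is clear on its own; the closed form carries the smaller ones.

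**5. Experimental-arm ICC, without v with age (true value 0.05).**

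| R² | Full sorting | Cohorts split in two | No sorting |
|---|---|---|---|
| 0 | 0.055 v 0.055 | 0.054 v 0.055 | 0.058 v 0.058 |
| 2% | 0.069 v 0.053 | 0.075 v 0.064 | 0.057 v 0.058 |
| 5% | 0.102 v 0.061 | 0.088 v 0.058 | 0.060 v 0.061 |
| 10% | 0.148 v 0.058 | 0.118 v 0.059 | 0.054 v 0.059 |

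For a later trial with groups of 7, the design effect is 1 + 6 × ICC. At R² of 5% it is 1.61 v 1.37 under full sorting (ratio 1.18) and 1.53 v 1.35 with split cohorts (ratio 1.13).

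**The case against.** - **No figure for age.** Baseline ADHDRS-PI is already in the model, so only what age adds beyond it counts. The article says nothing about that share. This stands, and the point has to be conditional.
- **Accrual limits sorting.** Section {15} targets 1–2 families per month per center: 12–24 a year, or 6–12 per arm. With groups of 7 that is about one or two groups per arm per center and year. A split cohort of 14 experimental children needs about 28 families, slightly more than a year's accrual, unless groups are smaller. This stands: the sorted scenarios lie toward the upper end, and with one group per cohort the ICC is not inflated. Sorting is nevertheless the stated rule.
- **One arm only?** A reader might infer that control groups are unsorted. The article is silent, and it is a condensed text. A parent-only program gives less reason to sort by child age, but silence does not establish an asymmetry.
- **The primary test?** A reader might infer that the main comparison is affected. The Student's or Mann-Whitney test has no cluster term and is not.
- **An ICC that is simply too high?** Vocabulary and techniques are adapted to each group's age level, so part of the difference between age-formed groups may be delivery. A later trial that forms groups the same way and omits age would want the unadjusted value. This stands, and is why both should be reported.
- **A matter for the analysis plan.** Further covariates are often left there. But {20a} does name an adjustment set, and {20b} promises ICCs from these models.

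**Conclusion.** The point holds in conditional form. To the extent that age predicts the 5-month score beyond baseline, and that accrual lets groups be sorted, the multilevel model counts age composition as therapy-group variance. Where sorting occurs, its standard error is about 1–3% larger than with age at R² of 1–2%, 6–7% at 5% and 12–15% at 10%, with no difference at 0. Of this, roughly 0.5–1%, 2% and 4% is ordinary covariate gain and no fault of the plan. The experimental-arm ICC rises by about 0.01–0.02, 0.03–0.04 and 0.06–0.09 over the same steps. These sizes rest on the assumed ICC of 0.05, groups of 7 and unsorted control groups.

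The error is conservative. A reader might infer a biased treatment effect or an inflated type I error; neither follows, because the groups are formed within arms after randomization and the standard error errs on the large side. Nor does the article show that the loss is large: the likely size is unknown from it.

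**What to change.** In {20a} and {20b}, prespecify the child's age at baseline as a fixed covariate in the multilevel models for the primary and secondary outcomes. Report the ICCs by arm, both with and without age adjustment, and say that experimental groups were formed by age and school level so that later users can choose the value that suits their design. A linear age term may leave some effect of school level behind; the two ICCs side by side make the effect of the age adjustment visible.

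The cost is one degree of freedom and slightly more reporting. Year of birth is already part of patient identification at inclusion ({16b}). The article reports recruitment as still open and analysts as seeing only groups A and B, so the change can be fixed without unblinding. The sample size and the Student's test do not change.

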**Methods:**

Two hundred forty-eight children diagnosed with ADHD will be randomly assigned to either a Hyper-mCBT program or a Barkley program. This is a multicenter randomized (1:1), 2 parallel-group, superiority trial with evaluator blinding and stratification according to center and methylphenidate treatment. The Hyper-mCBT program consists in a series of 16 simultaneous-but-separate therapy sessions for parents and for children.

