### Trial design {8}

This is a randomized (1:1), two parallel-group, multicenter superiority trial with evaluator blinding and stratification according to center and methylphenidate treatment. Randomization is based on families, not on individual children.

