## Assignment of interventions: allocation

### Sequence generation {16a}

Families are randomized to either study arm in a 1:1 ratio. Randomization lists consisting of centralized randomly sized blocks are established per center. These lists are the responsibility of an independent methodologist at the BESPIM. A specifically designed SAS program (Cary, NC, USA) is used to carry out randomization.

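### Center and methylphenidate are named as stratification factors, but the stated primary analysis includes neither, and the description of the randomization lists does not mention methylphenidate

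*Protocol article*

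**What the plan says.** Trial design {8} describes a "multicenter superiority trial with evaluator blinding and stratification according to center and methylphenidate treatment". The Methods paragraph of the abstract names the same two factors: "superiority trial with evaluator blinding and stratification according to center and methylphenidate treatment".

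Sequence generation {16a} gives the allocation ratio ("Families are randomized to either study arm in a 1:1 ratio") and then says: "Randomization lists consisting of centralized randomly sized blocks are established per center". Methylphenidate does not appear there.

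Statistical methods {20a} fixes the endpoint: "The primary outcome is the change from baseline in the ADHDRS-PI at 5 months". The first-named comparison is simple: "A Student’s test will be used to compare the two groups", with Mann-Whitney as the fallback. A multilevel mixed model of the 5-month score then completes it, estimating the treatment effect "by adjusting for cluster effects and ADHDRS-PI score at baseline". The clustering described there is correlation among people treated in the same therapy group. Methods for additional analyses {20b} extends the same kind of methods to the secondary outcomes and adds no covariate.

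**The concern.** An analysis should reflect the restrictions placed on the randomization. Stratified blocks force the arms to be nearly balanced on the strata, so differences between strata drop out of the treatment contrast. A test that ignores the strata still counts those differences as noise. If the factors predict outcome, its standard error is too large: it rejects a true null hypothesis less often than 5% and gives up some power.

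The article itself makes methylphenidate a plausible predictor. Its background section credits drug treatment with the larger effect on symptoms, and its eligibility section admits both treated and untreated children.

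The description of the lists matters because the consequence depends on it. If methylphenidate was a stratum, the issue is conservatism. If it was not, that factor's balance was left to chance, and adjustment would serve to correct imbalance and gain precision.

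**Working it through.** **1. The stated sample size.** Inputs from Sample size {14}: difference 9, SD 20.6, two-sided 5%, power 90%, 10% loss.

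- n per group = 2 × (20.6 × (1.960 + 1.282) / 9)² = 110.1, rounded up to 111.
- 111 / 0.90 = 123.3, rounded up to 124; 2 × 124 = 248.
- Power at 111: 9 / 20.6 = 0.4369; 0.4369 × √(111/2) = 3.255; Φ(3.255 − 1.960) = Φ(1.295) = 90.2%.

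The stated 111, 124 and 248 are reproduced. The calculation compares two means with no allowance for strata.

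**2. If both factors were stratified.** Let R² be the share of outcome variance that center and methylphenidate explain together. The article gives no value, so 5, 10 and 20% are assumed. With balanced strata, the true standard error is the nominal one times √(1 − R²), while the unadjusted test keeps using the nominal one.

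- Type I error, unadjusted: 2 × [1 − Φ(1.960 / √(1 − R²))]
- Power, unadjusted: Φ((3.255 − 1.960) / √(1 − R²))
- Power, adjusted: Φ(3.255 / √(1 − R²) − 1.960)

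For R² = 10%, √0.90 = 0.9487. Type I error uses 1.960 / 0.9487 = 2.066, giving 3.9%. Unadjusted power is Φ(1.295 / 0.9487) = Φ(1.365) = 91.4%. Adjusted power is Φ(3.431 − 1.960) = Φ(1.471) = 92.9%.

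| R² (assumed) | Type I error, unadjusted | Power, unadjusted | Power, adjusted | Power lost |
|---|---|---|---|---|
| 0% | 5.0% | 90.2% | 90.2% | 0 |
| 5% | 4.4% | 90.8% | 91.6% | 0.8 points |
| 10% | 3.9% | 91.4% | 92.9% | 1.5 points |
| 20% | 2.8% | 92.6% | 95.3% | 2.7 points |

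**3. Check by simulation.** Assumptions: 4,000 replicates, 222 analysed, three equally likely centers, half the children on methylphenidate, R² shared equally between the two factors, blocks of 4 and 6. The simulation error on a 5% rate is √(0.05 × 0.95 / 4000), about 0.3 points.

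| Lists | R² | Type I error, unadjusted / adjusted | Power, unadjusted / adjusted |
|---|---|---|---|
| Center and methylphenidate | 10% | 3.8% / 5.1% | 91.4% / 92.9% |
| Center only | 10% | 5.0% / 5.4% | 89.4% / 91.8% |
| Center only | 20% | 4.2% / 5.2% | 91.6% / 95.3% |

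With lists by center alone, the unadjusted test is close to nominal at R² = 10% and mildly conservative at 20%, since center is still balanced. Adjustment still gains precision.

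**4. If methylphenidate was not stratified.** With half the children treated (assumption), the SD of the difference between arms in the proportion on methylphenidate is √(2 × 0.5 × 0.5 / 124) = 0.063, or 6.3 percentage points.

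None of these figures allows for therapy-group clustering. The simple test ignores that too, and it pushes type I error in the opposite direction.

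**The case against.** **The analysis plan may add the factors.** It may. But {20a} does not leave the model open: it names the test and lists the adjustment terms, and the two design factors are not among them. For the repeated-measures model, {20b} lists no covariates at all, which is ordinary detail for an analysis plan, and I make no point of it.

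**The lists may be correct.** A reader might infer that {16a} restricts the lists to center alone and so contradicts {8}. The text does not support that. It says the lists are per center and does not say that center was the only factor. Center lists subdivided by methylphenidate fit both sections. What stands is an incomplete description that needs reconciling.

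**A multilevel model might include a center level.** That is possible, but it is not stated, and methylphenidate would still be absent.

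**R² may be small.** This stands. The outcome is a change score and the model adjusts for baseline. Treated children are on a stable dosage, remain symptomatic and meet the same entry score as the others. Much of methylphenidate's influence on symptom level may already be in the baseline score. Nothing in the article supports a value as high as 20%.

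**No bias and no excess of false positives arises from the omission.** This also stands. Even without stratification on methylphenidate, the nominal error rate of a randomized comparison already covers chance imbalance.

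**Conclusion.** The mismatch is real and modest. Two factors are declared for stratification, neither appears in the stated primary analysis, and the section on the lists mentions only one.

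If both were stratified and are prognostic, the cost is a conservative test before clustering: type I error of about 4.4, 3.9 or 2.8%, and 0.8, 1.5 or 2.7 points of power, at assumed R² of 5, 10 or 20%. The estimate is unbiased and the sample size of 248 needs no change. If methylphenidate was not stratified, type I error is close to nominal, and adjustment is worth having for chance imbalance and precision.

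Two stronger readings are tempting and do not hold. First, a reader might infer that adjustment lifts power from 90% to 92–95%. That sets adjusted power at positive R² against unadjusted power at R² = 0. At the same R², the unadjusted test already has 90.8 to 92.6%. Second, a reader might count both the conservative type I error and an uncontrolled methylphenidate imbalance as harms. The tabulated type I errors require methylphenidate to have been stratified and the imbalance requires that it was not, so both cannot apply.

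**What to change.** In {20a}, make the multilevel model the single primary analysis, with baseline ADHDRS-PI, center as a fixed effect (three centers), baseline methylphenidate status and the therapy-group effect. Keep the Student's or Mann-Whitney test as supportive. Adding covariates to the model alone would not be enough, because the first-named unadjusted test would still read as the primary comparison. Use the same two factors in the models for secondary outcomes.

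Reconcile {8} and {16a} by checking the lists and stating the strata actually used. Keep methylphenidate status in the model whatever the check shows.

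The cost is a short rewording of {20a} and one correction in {16a} or {8}. The model spends three degrees of freedom, two for center and one for methylphenidate. Both variables should already be on record as declared stratification factors. The article reports recruitment still open at 171 of 248 and places analysis after the database is frozen, so on that timetable the change can be fixed before any comparison of outcomes.
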